## Background

Obtaining a basic educational degree increases the chances of finding a permanent skilled job and is associated to better health. Students who break off their education prematurely often find themselves in a more vulnerable situation with regard to developing illnesses, being unemployed and being involved in criminal activities, as compared to students who hold a basic educational degree. Reasons to drop out of school prematurely, as reported by students, vary from learning and motivation difficulties, behavioural, (mental) health problems to problems at home [1–5].

School absenteeism is often a precursor of school dropout and absenteeism in future careers [4, 6–10]. It can be divided into unexcused (truancy) and excused absenteeism. The most common form of excused absenteeism is absence due to sickness reporting or sick leave, so called medical absenteeism. Medical absenteeism is perceived twice as often as truancy among adolescent students [11]. Particularly at intermediate vocational educational schools, high rates of medical absenteeism and school dropout can be found. Of all students entering intermediate vocational education, only 50% passes on to the second year and after five years approximately 25% leaves school without a degree [12]. Investing in effective methods regarding the prevention of extensive medical absenteeism at intermediate vocational education schools is therefore relevant.

The Dutch Youth Health Care (YHC) system offers preventive health care for children and adolescents between 0 and 18 years old. It aims to foster the optimal trajectory for growth and development in children and to provide anticipatory guidance to prevent negative outcomes later in life [13]. In general, the YHC system does not focus actively on students with extensive medical absenteeism. The current policy of most intermediate vocational education schools does not include an active identification of students with extensive absenteeism and referrals to YHC professionals are limited [14, 15]. Because of the high rate of medical absenteeism at intermediate vocational education schools and the complex underlying problems, however, the YHC system could play an important role in addressing medical absenteeism [16–20].

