## Methods/Design

### Study design

A controlled before-and-after study with a follow-up period of 6 months will be conducted. Students with extensive medical absence attending schools in which the MASS intervention has been implemented (intervention group) are compared to students attending schools in which the MASS intervention has not been implemented (control group).

The Medical Ethical Committee of Erasmus University Medical Centre Rotterdam has declared that the Medical Research Involving Human Subjects Act (also known by its Dutch abbreviation WMO) does not apply to this research protocol and issued a declaration of no objection (i.e. formal waver) for this study (MEC-2015-614). Therefore, the study can be carried out without further approval by an accredited research ethics committee.

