### Participants

#### Youth health care organizations, schools and youth health care professionals

This study will be conducted in the Dutch regions of Amsterdam, Utrecht, West Brabant and Rotterdam. School recruitment will be organized in collaboration with three YHC organizations associated to the regions of Amsterdam, Utrecht and West Brabant. The YHC organization in Rotterdam will not be involved in the study as schools in this area have not yet implemented the MASS intervention and will therefore be allocated to the control group.

YHC organizations invite the intermediate vocational education schools to participate in the study. Schools that agree to participate will subsequently be visited by the researchers. It is expected that a total of 12 schools will participate. The allocation of the schools will be based on their current policy. Schools will be classified as an intervention school (IS) or as a control school (CS) based on their current use of the MASS intervention.

All YHC professionals of participating intervention schools will be offered a training in the MASS intervention at the start of the study.

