#### Students

Students of participating schools are included in the study if they meet the criteria for extensive medical absenteeism, which is based on the MASS intervention at pre-vocational secondary education schools (i.e. reported sick for at least four times in 12 weeks or reported sick for more than six consecutive school days). We expect to include a total number of 480 students in the study with an equal distribution between the control and intervention group (see Fig. 1).

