### Intervention

#### Intervention group: the MASS intervention

The MASS intervention designed for intermediate vocational education schools consists of five steps: an active approach by the school after the first sick report, a meeting between student and school, a YHC professional referral if needed, the actual YHC professional consultation, and the further monitoring of the medical absenteeism and reintegration of the student [31] (Table 1).

**Table 1 Tab1:** Description of the key steps of the MASS intervention

Step	Description
1	The school contacts the student actively in case of medical absence and asks about the context of the sickness report and condition of the student.
2	The school organizes a meeting with the student (and parents if student is <18 years old) in case of extensive medical absenteeism (criteria predefined by each individual school, apart from the MASS criteria).
3	The school refers the student to a YHC professional if considered to be needed.
4	A YHC consultation between student and YHC professional is organized
5	The school is responsible for monitoring the medical absenteeism and school-related implementation of the reintegration plan, if created.

*MASS* Medical Advice for Sick-reported Students

*YHC professional* Youth health care professional

The intervention focuses at two levels; the school level and the individual level. The implementation of the MASS intervention at school level includes agreements on how to actively monitor student absence, approach students with extensive medical absence by personal contact, request a consultation with the YHC professional, and arrange a follow-up for each student in the Care Advisory Team (CAT). The CAT includes social workers, attendance officer, YHC professionals, teachers and a Youth Care Office representative.

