### Statistical analyses

In order to evaluate effect of the effect of the intervention the scores on outcomes of both groups measured during follow will be compared, adjusted for baseline findings. For continuous outcome measures such as duration of the medical absenteeism and psychometric test results (multiple) linear regression analyses will be applied. Dichotomous outcomes, such as progressing into the next year or obtaining a basic educational qualification degree, will be evaluated by using a multiple logistic regression analysis.

The research condition will be included as an independent variable. Baseline values of the outcomes are added to the model as covariates. As students are clustered within school locations multilevel analyses will be applied.

Potential moderation of intervention effects by gender, family situation, ethnicity, psychosocial and psychiatric problems (depression, drug abuse, ADHD) is explored by adding an interaction term to the regression models. Stratified analyses will be performed when significant interactions (*p* < 0.10) are observed.

Experiences of students and YHC professionals with the different elements of the MASS intervention as performed by YHC professionals will be evaluated by performing descriptive analyses.

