## Discussion

Medical absenteeism is positively associated to early school dropout and may result in physical, mental, social and work-related problems later in life. The aim of the MASS intervention is to limit the medical absenteeism of students by arranging appropriate care, educational adjustments and adequate support [19, 21]. This paper describes the design of a controlled before-and-after study, which aims to evaluate the effectiveness of the MASS intervention as well as its contributing factors and interfering factors among intermediate vocational education school students.

It is hypothesized that implementation of the MASS intervention and incorporating a referral to a YHC professional is effective in terms of reducing medical absenteeism. Results of this study will show whether the YHC professional added value in the MASS intervention. Moreover, the study will provide insight in which factors contribute and/or moderate to the intervention’s effectiveness and may provide useful suggestions for improvement.

A strength of this study is that it will be conducted in the daily setting schools and YHC practice, which will facilitate future implementation. The participating schools and YHC professionals cover the urban and rural areas of the Netherlands, which will support the generalizability of our findings. Nevertheless, the schools and students are not randomized which can result in differences between the groups. We have tried to minimize this potential effect by correcting for potential confounders. Another strength is that we look at the extent to which the MASS intervention is applied by de YHC professional and gain insight into the care provided by the school to the individual students.

As the MASS intervention had already been implemented at the intervention schools, we could not capture strict criteria for referral to the YHC professional. The criteria for referral to a YHC professional were determined by each individual school which is in line with the MASS protocol, which may result in a variety of used criteria. On the other hand, this will give a realistic approach of the effects of the implementation of the MASS intervention. Also, the MASS-protocol requires great commitment of the schools to identify and refer students to YHC professionals [43]. It is therefore questionable how many students eventually will be identified and/or referred to the YHC professional.

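### Entry and baseline absence already arise under MASS at the intervention schools, so the T0-adjusted comparison cannot estimate the effect of implementing MASS

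*Protocol article*

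**What the plan says.** - **Design label.** Study design: "A controlled before-and-after study with a follow-up period of 6 months will be conducted".
- **Allocation.** The section on organisations, schools and professionals: "Schools will be classified as an intervention school (IS) or as a control school (CS) based on their current use of the MASS intervention". The Discussion confirms the timing: "As the MASS intervention had already been implemented at the intervention schools".
- **Start of exposure.** The section on the intervention group lists five steps, the first being "an active approach by the school after the first sick report". Step 2, a meeting with the student, follows "criteria predefined by each individual school, apart from the MASS criteria".
- **Entry.** Students: a student qualifies when "reported sick for at least four times in 12 weeks or reported sick for more than six consecutive school days".
- **Baseline.** Data collection takes absence hours from the school register for the 12 weeks before T0 and before T1.
- **Model.** Statistical analyses: "Baseline values of the outcomes are added to the model as covariates".
- **Claim.** The hypothesis in the Abstract and the Discussion concerns implementing MASS. The aim in the Background concerns the effectiveness of MASS, with emphasis on the youth health care professional. The closing paragraph of the Discussion speaks of students with high absence who receive a reintegration plan, and leaves an evaluation of full implementation for later.

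**The concern.** A controlled before-and-after design needs a measurement in the intervention group from before the intervention. None is planned here. T0 is the point at which a student enters, in a school that already runs MASS.

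The order of events matters. At an intervention school, contact starts at the first sick report, and the step 2 meeting may also come before study entry because each school sets its own trigger. Entry needs at least four reports or more than six consecutive days. Any student whose absence early contact cut short never qualifies, and those who do qualify got there despite that contact. The T0 hours were accrued under MASS in one arm only, and the model then conditions on them.

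Whatever MASS achieves before entry thus lies partly in the covariate and partly in who becomes eligible. The analysis does not count it. A small or null adjusted difference could be read as showing that MASS does not work, when the comparison did not test MASS as a whole. The Discussion mentions prior implementation only to explain why referral criteria vary between schools.

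**Working it through.** **1. The plan's own figure.** Inputs from Power considerations: 120 analysed per group, intraclass correlation 0.10, 15 students per class, SD 30 h, one-sided alpha 0.05, power 0.80.

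- Design effect: 1 + (15 − 1) × 0.10 = 2.4. Effective size: 120 / 2.4 = 50 per group.
- Detectable difference: 30 × √(2 × 2.4 / 120) × (1.645 + 0.842) = 14.92 h, against the stated 15 h.
- Power at 15 h: 0.804.

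The power arithmetic reproduces and is not in question.

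**2. What the adjusted coefficient estimates.** Let D1 be the total MASS effect on absence before T1, D0 the part already present in the 12 weeks before T0, and ρ the T0–T1 correlation, with equal SDs. In a linear regression of T1 on group and T0, the expected group difference is D1 − ρ·D0.

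D1 = 15 h is the plan's detectable difference, used here as an assumed true effect. D0 and ρ are not in the document, so a range is shown.

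| D0 as share of D1 | ρ = 0.3 | ρ = 0.5 | ρ = 0.7 |
|---|---|---|---|
| 0% | 15.0 h | 15.0 h | 15.0 h |
| 25% | 13.9 h | 13.1 h | 12.4 h |
| 50% | 12.8 h | 11.3 h | 9.8 h |
| 100% | 10.5 h | 7.5 h | 4.5 h |

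Example: ρ = 0.5 and D0 = 7.5 h gives 15 − 0.5 × 7.5 = 11.25 h.

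**3. Consequence for power at ρ = 0.5.** For D0 of 0, 25, 50 and 100% of D1, power is 0.80, 0.71, 0.59 and 0.35 with SD 30 h. With the residual SD of 30 × √(1 − 0.5²) = 26.0 h it is 0.89, 0.81, 0.70 and 0.42.

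**4. Simulation check.** One million students per group, with eligibility assumed to be the top 20% of control-school T0 hours.

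- The adjusted estimates match the formula (7.5 h at ρ = 0.5, D0 = D1).
- The eligible share at MASS schools falls from 20% to about 17%, 14% and 9% for D0 of 25, 50 and 100% of D1.
- Without T0 in the model, the contrast among eligible students at ρ = 0.5 and D0 = D1 is 9.0 h, still below 15 h. Dropping the covariate would not cure the problem.

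In this linear model, selecting on T0 hours does not itself alter the adjusted coefficient. The simulation therefore confirms the formula and shows the change in who qualifies, but it does not measure selection bias. The real entry rule counts reports or consecutive days, not hours.

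**The case against.** Much of the text already leans towards the narrower question. The aim stresses the youth health care professional, which is a later step. Study design defines the comparison among students with extensive absence. The closing paragraph defers full implementation to a later evaluation. The before-and-after label also has a student-level reading, since the first primary outcome compares T1 with T0. This stands in part: the fault is inconsistency as well as over-reach. But the hypothesis still speaks of implementing MASS, and nothing requires T0 to precede the school meeting or the consultation.

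A reader might infer two stronger things that the document does not support.

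- **That the result is biased towards no effect.** If early contact lowers T0 absence, that mechanism alone attenuates the estimate. But schools that monitor absence actively may also bring in milder cases, which could favour MASS. The Background remark that the policy of most schools "does not include an active identification of students with extensive absenteeism" describes routine practice, not study procedure. Under Procedure, coordinators at all schools select on the same criterion. Identification may differ, but neither its size nor its direction can be read from the text.
- **That differences between schools are left uncontrolled.** Baseline outcomes and other covariates are planned, and the Discussion admits the lack of randomisation. In such a study T0 absence is an important confounder control and cannot simply be removed. Unmeasured school differences remain, as the authors say.

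**Conclusion.** The point holds. Intervention schools are defined by already using MASS, exposure begins before entry, and both eligibility and T0 absence arise under MASS in one arm only. The planned contrast therefore cannot estimate the effect of implementing MASS. At best it estimates what MASS adds once a student has reached the criterion.

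The size is conditional. The loss relative to D1 is ρ·D0: nothing if early contact has no effect, and between 7.5% (0.3 × 25%) and 70% (0.7 × 100%) over the remaining cells of the table. D0 and ρ are assumptions, and the formula covers only the covariate mechanism. The net direction of bias is not established.

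**What to change.** 1. **Rename and restate.** Describe the design as a non-randomised controlled cohort in schools with and without MASS. State the aim, hypothesis and conclusion consistently as the effect of MASS from the moment a student reaches the criterion. Keep T0 adjustment as confounder control. Add that T0 and eligibility arise under MASS at intervention schools, so a null result does not show that MASS as a whole is ineffective. Cost: wording only.
2. **Identify students in one way.** Run one identical query of the absence register, on the stated criterion, at every school. Invite every student it returns, and report by group the share of students who reach the criterion. Cost: a shared query definition and some coordinator time; the registers already supply the absence data.
3. **Optional.** Where available, request aggregate absence per school from before MASS began, with the same calendar period at control schools, as a supportive school-level comparison. With about 12 schools it will be imprecise, and some schools may not have the data.

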## Abbreviations

CAT: Care Advisory Team
CES-D: Centre for Epidemiologic Studies Depression scale
CS: Control school
IS: Intervention school
MASS: Medical Advice for Sick-reported Students
SF-12: 12-item Short Form Health Survey
T0: Baseline questionnaire
T1: Follow – up questionnaire
YHC: Youth Health Care
